#### Institutional review board (IRB) approval and ethical treatment of participants

All procedures were reviewed and approved by the IRBs of University of California at San Diego, Population Council and India’s National Institute for Research in Reproductive Health. NIRRH led oversight of research procedures in the field to monitor and ensure ethical treatment of participants and adherence to study protocol. This study was registered at clinicaltrials.gov (NCT01593943).

A data and safety monitoring plan was also in place and focused on two major safety aspects: 1) assurance that no harm came to participants as a result of survey or program participation and 2) assurance that all data collected from this project, including process and quality assurance data as well as outcome data, would maintain the privacy of research participants. To ensure no harm, and with recognition of high rates of domestic violence in India, at the time of each survey data collection, participants were assessed for immediate health and social service needs in the areas of FP, maternal or antenatal health, and violence, by research staff trained to provide referrals and links to health and social services, in accordance with the WHO guidelines for ethical research on domestic violence [37]. Participants were also notified via informed consent that their withdrawal from the program would not affect their participation in the survey participation and vice versa. Also, withdrawal from both the program and the survey participation would have no impact on the services they received at the local health clinic or within their work organization. Through informed consent, participants were additionally notified of research staff they could contact should any difficulties arise through their participation in this project. We did not anticipate that the surveys or medical record reviews would cause harm to enrollees, but the IRBs from all partnering institutions involved in this study (NIRRH, ICMR, Population Council and UCSD) had strict reporting requirements for adverse events and a yearly reporting process with which we complied with at all times. Multiple efforts were made across all study phases to reduce risks for adverse events. However, a data and safety monitoring plan was used to identify such events if they did occur. The plan was as follows: Should an adverse event be identified, the principal investigators from each site were to be notified within 48 h, and then there was to be a discussion that week whether the adverse event had anything to do with the research study (e.g., a death due to subject’s occupation), or whether it occurred as a consequence of an individual’s study participation (e.g., abuse of a participating wife subsequent to intervention involvement). IRBs and funders were to be notified immediately following the discussion. If it were the latter, considerations of how to reduce such risks in the future were to be determined and protocols were to be altered accordingly. No adverse events occurred, so the plan never required operationalizing.

Data security and confidentiality were also a priority of this study. As noted above, all data were de-identified, and participant identifiers such as name or location were maintained on separate forms in locked storage at a different location from the analytical database. Only field staff and their supervisor, a member of the scientific team, had access to the linked information. Data shared between investigators across countries were maintained on secure servers that only allow connections from users authenticated from the domain controller. Password protection also locked individual data fields. In terms of data management, all hard data collected from this study was brought to a field office for data entry, coding, management and analysis. Hard data safety was assured by locking the collected data, consent forms, contact numbers and addresses in separate securely locked cabinets in a locked office that was only accessible to the field supervisor. Electronic data files (e.g., survey data collected via tablets) were maintained on secure servers and labeled only by unique identifiers. If any security arrangement had been violated, either through physical tampering or breach of confidentiality, the individual making the discovery were to notify the Principal Investigators, and it would have been handled as an adverse event, but as noted above, no issues arose. We believe the risks to the subjects were reasonable in relationship to the anticipated benefits.

#### Sample size calculation

Sample size and power considerations were constructed based on our primary outcomes of interest: any spacing contraceptive use and communication. As noted above, unmet need was an original outcome of the study, but our item measures did not allow for an accurate assessment of this variable. A baseline sample size of 1000 couples, equally distributed between the 50 clusters/villages, as well as equally distributed between the intervention and the control groups was assumed. We also assumed 20 % attrition (at the end of 18-months of follow-up) and thus, based our calculations on 800 men. All calculations were based on 2-sided logistic regressions with a significance level of 0.05. While we utilized longitudinal regression methods in our analyses, for the purposes of power calculations we utilized single time-point methods. However, considering general longitudinal analyses yield higher power, this should not be a problem. Furthermore, due to the cluster randomization of the proposed study, our computations were adjusted for the design effect in order to account for the correlation of subjects within the same village. Assuming 20 men enrolled in each village, and a within village correlation (Kappa) of 0.10, the design effect [1 + within village correlation*(# of men per village-1)] was estimated to be equal to 2.9. We should note that the assumed kappa value of 0.10 is within the range of what is often observed in clinical studies, and may be considered a conservative assumption given that we adjusted for potential village level confounders in the regression models. Below, we present power calculations to assess the minimum differences we aimed to detect with 80 % power for the primary endpoints of each outcome. The estimates used for these calculations came from NFHS-3 data on young married rural Maharashtrian men [1].

*Hypothesis 1:* This hypothesis tests the effect of intervention on the use of marital spacing contraceptives. Power calculations were based on Logistic Regression of a dependent binary variable (i.e. use of marital spacing contraceptives) on a binary independent variable (i.e. Group 1 = Intervention Group, Group 2 = Control Group) with 800 subjects equally distributed between the two groups. Referring to the power curves in Fig. 3, if the proportion of men reporting use of contraceptives in Group 2 is 8 %, 10 %, or 12 %, then we will have over 80 % power to detect a difference between Group 1 and Group 2, when the corresponding proportion in Group 1 is 20 % (OR_Group1/Group2_ = 2.8), 22 %(OR_Group1/Group2_ = 2.59), and 25 %(OR_Group1/Group2_ = 2.45), respectively. Based on the NFHS-3 data, we expected that the proportion of men using any marital spacing contraception in the control group (Group 2) would be 10 % at 18 months. Based on the above assumptions, the proposed study had 80 % power to detect an absolute difference as small as 12 % between the two groups. A difference of 12 % is considered clinically meaningful.

*Hypothesis 2:* This hypothesis tests the effect of intervention on any pregnancy at 18 month follow-up. Power calculations were based on Logistic Regression of a dependent binary variable (i.e. reporting pregnancy at 18 month follow-up) on a binary independent variable (i.e. Group 1 = Intervention Group, Group 2 = Control Group). Referring to the power curves in Fig. 4, if the proportion of men reporting pregnancy for wives at 18-months in Group 2 is 14 %, 16 %, or 18 %, then we would have over 80 % power to detect a difference between Group 1 and Group 2, when the corresponding proportion in Group 1 is 4 % (OR_Group1/Group2_ = 0.28), 6 % (OR_Group1/Group2_ = 0.31), and 7 % (OR_Group1/Group2_ = 0.34), respectively. Based on the NFHS-3 data, we estimated that the proportion of men reporting any pregnancy for wives at the 18 month follow-up in the comparison group would be 16 %. The proposed study had 80 % power to detect an absolute difference of at least 10 % between the control and intervention groups (Fig. 5).

**Fig. 4 Fig4:**
[figure not shown]
Power to detect the effect of intervention on use of marital spacing

**Fig. 5 Fig5:**
[figure not shown]
Power to detect the effect of intervention on pregnancy

#### Analytic plan

Outcome analyses were designed to focus on the following outcomes of interest: spacing contraceptive use and communication, and included pregnancy, intimate partner violence and attitude outcomes based on women’s reports and pregnancy testing. The primary comparison of the outcomes by treatment group at 9 and 18 month follow-ups were done using mixed-effects regression models, with a nested random effects structure for the geographical clusters and for each couple within the cluster, over time. The treatment effect was evaluated via a time-by-treatment arm interaction. A categorical time effect was used (profile model). This treatment effect can be interpreted as the individual-level effect of the intervention. In addition, generalized estimating equations (GEE) logistic regression models with the same clustering and mean model structure and exchangeable working correlation matrix was used to express the intervention effect at the population level. Secondary analyses adjusted for relevant covariates to improve precision and possibly reduce bias. Demographic and fertility variables (e.g., age, current pregnancy, past year childbirth, etc.) were considered for inclusion in adjusted analyses, in addition to time and treatment arm, using backward model selection at the 0.15 threshold level. Bivariate analyses were conducted to assess differences in demographics, fertility history, and outcomes at baseline: 1) by treatment group, 2) for those lost to study follow-up, and 3) for CHARM participants lost to intervention. Any characteristics identified as significantly different between groups were considered as potential covariates in these adjusted models. Outcome analyses used an intent-to-treat approach and analyzed all subjects according to randomized group. Additional analyses were conducted based on receipt of intervention. All analyses used women’s data only, but men’s data will be used to validate findings on contraceptive behavior outcomes. All analyses were conducted using SAS (SAS Institute, Version 9.4, Cary, NC, USA).

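### The time-by-arm interaction is not sure to have more power than the single-time-point test that was powered; that depends on a correlation the protocol does not give, and baseline adjustment would be more precise

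*Protocol article*

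**What the plan says.** Protocol article, Sample size calculation:

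- "All calculations were based on 2-sided logistic regressions with a significance level of 0.05", for one time point.
- Sample: "We also assumed 20 % attrition (at the end of 18-months of follow-up) and thus, based our calculations on 800 men", "with 800 subjects equally distributed between the two groups". With 20 men per village and a within-village correlation of 0.10, the design effect is 2.9.
- Spacing contraception: the expected proportion "in the control group (Group 2) would be 10 % at 18 months", and "the proposed study had 80 % power to detect an absolute difference as small as 12 % between the two groups", that is 22 % against 10 %.
- Pregnancy, 16 % against 6 %: "The proposed study had 80 % power to detect an absolute difference of at least 10 % between the control and intervention groups".
- On the gap between this calculation and the longitudinal analysis: "considering general longitudinal analyses yield higher power, this should not be a problem".

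Protocol article, Analytic plan: mixed-effects models with nested random effects for cluster and for couple within cluster. "The treatment effect was evaluated via a time-by-treatment arm interaction. A categorical time effect was used (profile model"). Time and treatment arm are both named as model terms, and nothing constrains the arms to be equal at baseline. Baseline must be one of the times, since an interaction over 9 and 18 months alone would not measure a treatment effect. The 18-month effect is therefore the arm difference in change from baseline.

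**The concern.** Power was calculated for one test and a different test carries the treatment effect. The only bridge between them is a general remark about longitudinal analyses. That remark suits analyses that average several follow-ups or adjust for baseline. A difference in change is another matter: subtracting the baseline adds its noise to the estimate, and this pays off only if baseline predicts follow-up well enough.

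Two things are at stake. The stated 80 % may not carry over to the test actually used. And on the primary outcomes the interaction is less precise than a baseline-adjusted contrast that needs no new data. The issue is precision and an unsupported power claim. It does not make the estimate invalid.

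**Working it through.** **1. The plan's own figure.** Effective total N = 800/2.9 = 275.9. For 22 % against 10 %, log OR = ln(0.2821/0.1111) = 0.932 and mean proportion P = 0.16. With var(log OR) = 1/[N P(1-P)/4] = 1/(275.9 × 0.1344/4) = 0.108, SE = 0.328, z = 2.84 and power = Φ(2.84 - 1.96) = 81.0 %. Pregnancy, 16 % against 6 %, gives 81.1 % in the same way. Other standard formulas give 76 to 79 % for contraception. The stated 80 % reproduces.

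**2. Variance of the test used.** Assume equal variances at both times, and let r be the correlation of cluster means between baseline and 18 months. Relative to the follow-up-only comparison:

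- interaction (difference in change): 2(1-r)
- baseline-adjusted at the level of cluster means: 1-r²
- baseline-adjusted relative to interaction: (1-r²)/[2(1-r)] = (1+r)/2

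The interaction breaks even where 2(1-r) = 1, so r = 0.5.

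**3. Break-even for binary outcomes.** Variances differ with the proportions. On the risk-difference scale, with 10 % at baseline in both arms and 22 % against 10 % at follow-up, the follow-up variance is proportional to 0.09 + 0.1716 = 0.2616. The difference in change has 0.4416 - 2r(0.09 + √(0.09 × 0.1716)) = 0.4416 - 0.4286r. These are equal at r = 0.42. The same steps on the logit scale give 0.58. For pregnancy (16 % at baseline) the values are about 0.61 and 0.39. So 0.5 is a centre and not a sharp line.

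**4. Power, starting from 80 % at a single time point.** Power = Φ(2.80/√v - 1.96), with v from step 2.

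| r (assumed) | Interaction | Baseline-adjusted |
|---|---|---|
| 0 | 51 % | 80 % |
| 0.2 | 60 % | 82 % |
| 0.4 | 72 % | 86 % |
| 0.5 | 80 % | 90 % |
| 0.6 | 88 % | 94 % |
| 0.7 | 95 % | 97.5 % |

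**5. Which r is plausible here.** With m couples per cluster, cluster autocorrelation CAC and couple-level autocorrelation SAC,

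r = [m·ICC·CAC + (1-ICC)·SAC] / [1 + (m-1)·ICC].

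The ICC of 0.10 and m = 20 are the protocol's; m = 16 is what 20 % attrition leaves. CAC and SAC are assumptions.

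| ICC | CAC | SAC | r (m = 16 to 20) |
|---|---|---|---|
| 0.10 | 1 | 0 | 0.64 to 0.69 |
| 0.10 | 0.8 | 0.2 | 0.58 to 0.61 |
| 0.10 | 0.5 | 0 | 0.32 to 0.35 |
| 0.02 | 1 | 0.2 | 0.40 to 0.43 |

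Simulated binary data (25 clusters per arm, 16 couples each, ICC 0.10, tests on cluster means) agree. With CAC 1 and SAC 0, power was 95 % for the interaction, 81 % for follow-up only and 96 % adjusted. With CAC 0.5 and SAC 0 it was 75 %, 79 % and 82 %.

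**6. Which adjustment delivers the gain.** The factor 1-r² needs the cluster-mean baseline. A couple-level covariate alone takes its slope mainly from within-cluster correlation. Simulated variances relative to follow-up only (linear outcome, one follow-up, 50 clusters of 18, ICC 0.10):

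| CAC, SAC | Interaction | Couple baseline only | Couple and cluster-mean baseline |
|---|---|---|---|
| 1, 0.2 (r = 0.73) | 0.49 | 0.70 | 0.45 |
| 0.5, 0.2 (r = 0.40) | 1.13 | 0.87 | 0.84 |

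In all six scenarios run, adjusting for both gave a smaller variance than the interaction. The gain in these two rows was 8 % (0.45/0.49) and 26 % (0.84/1.13), a little below the 13 % and 30 % from (1+r)/2.

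**The case against.** **The remark is true on the plan's own assumptions.** This stands. An ICC of 0.10 with time-constant cluster and couple intercepts puts r at 0.64 or more, and the interaction then beats the powered comparison. But a random-intercept model assumes stable cluster effects and gives no evidence of them over 18 months. The protocol itself calls 0.10 possibly conservative. If the ICC is smaller, single-time-point power starts above 80 %, yet the claim that the longitudinal test adds power can still fail.

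**The achieved sample has room to spare.** This also stands. With 891 couples at 18 months, m = 17.8, the design effect is 1 + 0.10 × 16.8 = 2.68 and the effective N is 332. The formula in step 1 then gives about 87 %, and the interaction at r = 0.4 has about 80 %.

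**Difference in change is defensible.** Clusters were allocated in February 2012, couples were recruited from March 2012, and staff were not blinded. Differential recruitment is possible, so the interaction deserves a place as a sensitivity analysis.

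**Stronger readings that the document does not support.** A reader might infer that the trial was underpowered, at 51 or 60 %. Those values need r of 0 to 0.2, which the protocol's own inputs do not suggest. A reader might infer that a couple-level correlation below 0.5 is enough to refute the remark; the correlation of cluster means decides. That applies to pregnancy too: a pregnancy present at baseline cannot persist to 18 months, so SAC should be weak, but r is still 0.64 or more if CAC is 1. Nor is the baseline wasted, since above break-even it helps. Nor is the 9-month wave useless for the 18-month contrast: with about 18 % missing at 18 months, a mixed model draws some information from it.

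**Conclusion.** The concern holds in a limited form. The interaction is a difference-in-change test with variance 2(1-r) relative to the comparison that was powered. The assurance of higher power is therefore conditional. It is correct if cluster effects are stable and the ICC is 0.10. It is wrong if r is below about 0.5 (0.42 to 0.58 for contraception, depending on scale). The document gives no r and so does not settle the matter.

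Separately, baseline adjustment that includes the cluster mean has about (1+r)/2 of the interaction's variance, that is 10 to 30 % less for assumed r of 0.4 to 0.8, with slightly smaller gains in simulation.

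These figures assume equal variances except in step 3, concern the 18-month contrast alone and not a joint test of both follow-ups, and rest on assumed autocorrelations.

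**What to change.** 1. In Sample size calculation, delete the remark on longitudinal power. Alternatively, give power for the interaction over a stated range of cluster- and couple-level autocorrelations, for contraception and for pregnancy.
2. In Analytic plan, for spacing contraceptive use and communication, model the 9- and 18-month responses with arm, time, arm-by-time, the couple's baseline outcome and the cluster-mean baseline outcome. Report the arm difference at each follow-up. Do not use the couple-level covariate alone, since it can be less precise than the interaction.
3. Keep the change-from-baseline interaction as a sensitivity analysis, because unblinded recruitment followed allocation.

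The cost is slightly more model specification and a small loss of degrees of freedom at cluster level. No new data are needed, as all 1,081 enrolled couples completed a baseline survey. The adjusted odds ratio is also conditional on baseline outcome, so its size should not be compared directly with the interaction's. Since the article reports all study procedures as complete, say when the adjusted model was fixed relative to sight of the results.

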#### Process evaluation

The process evaluation was designed to ensure quality delivery of the program and to assess response from participants and providers. To measure the quality of delivery and fidelity to program design, we did the following: 1) Provided standard training for all VHPs, as noted above, and conducted pre-post analysis after each session on FP and GE knowledge and attitudes, using these data to address in the next training session any gaps identified, 2) Required checklists and case sheets for each session delivered by the VHP to track session delivery, ensure coverage of all pieces of the intervention (indicated on the checklist), and assess issues that arose in the sessions for follow-up at next session or elsewise (using case notes), 3) Conducted clinical supervisory meetings with all VHPs on a monthly basis to discuss CHARM delivery and specific cases of concern, with review of VHP checklists and case sheets. CHARM VHP supervision was conducted jointly by preventive medicine and FP experts, 4) In-depth interviews with intervention VHPs and select study participants to provide feedback on their view of the intervention, as described above; and 5) Brief surveys conducted with intervention participants at follow-up to assess their perception of FP components of the program and their perceptions of the intervention, as noted above. (See Table 3 for details on each piece of process evaluation and how it was managed and analyzed.) Collecting these data enabled quality control by the research team and pragmatic feedback for the program staff to maintain quality delivery of the intervention across VHPs. Data collection related to this component were used to: a) ensure adherence to the intervention in terms of structure, content, and strategies; b) ensure that staff training and experience relevant to program implementation is consistent with the guidelines set for the intervention; and c) assess staff and subject response to the programs. Protocols and tools for this component were developed for this study.

**Table 3 Tab3:** Process evaluation components for CHARM project

Form	Who completes form and when	Who collects form and when	Purpose of form	How is data processed
1. VHP Checklist	Who: VHPs	Who: ^b^Data Manager will collect and give to ^b^Scientific Lead in the Field and ^b^Monitoring and Evaluation Manager	Quality control to ensure all activities were covered in each session. A one page checklist for VHPs to use to make sure they cover each piece.	Reviewed by ^b^Scientific Lead in the Field and ^b^Monitoring and Evaluation Manager, monthly; Feedback provided to VHPs in monthly meetings; Update provided to US Team Monthly during weekly conference call; entered into SPSS
- Individual Sessions	When: Just before the conclusion of each intervention session			
		When: Monthly.		
2. VHP Casesheet	Who: VHPs	Who: ^b^Data Manager will collect and give to ^b^Scientific Lead in the Field and ^b^Monitoring and Evaluation Manager	This sheet is for VHPs to assess participant's attitudes, knowledge around the family planning and gender equity issues; and provide necessary communication.	Reviewed by ^b^Scientific Lead in the Field and ^b^Monitoring and Evaluation Manager, monthly; Feedback provided to VHPs in monthly meetings; Update provided to US Team Monthly during weekly conference call; entered into SPSS
- Individual sessions	When: During each intervention session			
		When: Monthly.		
2. Final Participant Satisfaction Survey^a^	Who: CHARM Intervention Participants (male only). Conducted by field team	Field staff, at the end of endline survey (9 months post-baseline)	Participant satisfaction with CHARM intervention	Entered with quantitative data; prevalence data used for reports
	When: At time of endline/9 month survey.			
3. In-Depth Interviews with VHPs	Who: All CHARM VHPs subsequent to program completion. IDIs will be conducted by field team	Field staff, after the 9 months follow-up but before the 18 month follow-up.	Feedback on perceptions of strengths and weaknesses of CHARM in terms of recruitment, retention, intervention delivery and mechanisms of outcome effects.	Transcribed/translated and analyzed by field team using Atlas-ti.
		Note: All VHPs should be interviewed if they provided at least one session.		
	When: Subsequent to completion of study.			
4. In-Depth Interviews with Male Participants and Female Participants	Who: CHARM Intervention Participants only (both male and female participants). 10 % of all participants randomly selected for inclusion **as couples, among those completing all three sessions**.	Field staff, after intervention delivery for the couple is over, at a survey follow-up assessment.	Feedback on perceptions of strengths and weaknesses of CHARM in terms of recruitment, retention, intervention delivery and mechanisms of outcome affects.	Transcribed/translated and analyzed by field team using Atlas-ti.
	When: At 9 or 18 month follow-up.			

^a^
*form is data entered*

^b^Indicates name was removed and replaced with title of position

Additional data: Notes taken at monthly meetings b/w Indian intervention team will be conveyed during Indo-US weekly meetings to check ongoing issues and implementation. Meeting notes from Indo-US meetings will be maintained for review

